## Abstract

**Background:**

Major Depressive Disorder (MDD) is one of the most prevalent psychiatric disorders, and involves high relapse rates in which persistent negative thinking and rumination (i.e., perseverative cognition [PC]) play an important role. Positive fantasizing and mindfulness are common evidence-based psychological interventions that have been shown to effectively reduce PC and subsequent depressive relapse. How the interventions cause changes in PC over time, is unknown, but likely differ between the two. Whereas fantasizing may change the valence of thought content, mindfulness may operate through disengaging from automatic thought patterns. Comparing mechanisms of both interventions in a clinical sample and a non-clinical sample can give insight into the effectivity of interventions for different individuals. The current study aims to 1) test whether momentary psychological and psychophysiological indices of PC are differentially affected by positive fantasizing versus mindfulness-based interventions, 2) test whether the mechanisms of change by which fantasizing and mindfulness affect PC differ between remitted MDD versus never-depressed (ND) individuals, and 3) explore potential moderators of the main effects of the two interventions (i.e., what works for whom).

**Methods:**

In this cross-over trial of fantasizing versus mindfulness interventions, we will include 50 remitted MDD and 50 ND individuals. Before the start of the measurements, participants complete several individual characteristics. Daily-life diary measures of thoughts and feelings (using an experience sampling method), behavioural measures of spontaneous thoughts (using the Sustained Attention to Response Task), actigraphy, physiological measures (impedance cardiography, electrocardiography, and electroencephalogram), and measures of depressive mood (self-report questionnaires) are performed during the week before (pre-) the interventions and the week during (peri-) the interventions. After a wash-out of at least one month, pre- and peri-intervention measures for the second intervention are repeated.

**Discussion:**

This is the first study integrating self-reports, behavioural-, and physiological measures capturing dynamics at multiple time scales to examine the differential mechanisms of change in PC by psychological interventions in individuals remitted from multiple MDD episodes and ND individuals. Unravelling how therapeutic techniques affect PC in remitted individuals might generate insights that allows development of personalised targeted relapse prevention interventions.

**Trial registration:**

ClinicalTrials.gov: NCT06145984, November 16, 2023.

**Supplementary Information:**

The online version contains supplementary material available at 10.1186/s12888-024-05592-8.

## Background

Major Depressive Disorder (MDD) is one of the most prevalent psychiatric disorders affecting about 20% of the world population at some point in their life [1, 2]. The risk of a relapse after suffering from a depressive episode is high (40–60% after recovering from a first episode [3–5]. Therefore, lowering relapse vulnerability is an important therapeutic target. Understanding how specific psychological interventions affect core vulnerability factors is a potentially powerful way to improve individual patient’s relapse prevention.

Ruminative thinking is one of the core factors creating high vulnerability for relapse as rumination and related worrying have been identified as key processes in developing and maintaining MDD [6, 7]. MDD patients report more negative, past-related, and self-related spontaneous thinking compared to healthy individuals [8]. MDD patients also frequently engage in ruminative thinking, characterized by repetitive, negative, and uncontrollable thoughts that are difficult to disengage from [9]. This type of thinking can also be put under the umbrella term ‘perseverative cognition’ (PC) [6, 10]. PC often remains after remission from a depressive episode and is a common residual symptom (e.g., [7, 11]). Because of its relation with depressive relapse [7, 12], targeting PC in the remitted stage of MDD could be a powerful way of preventing the recurrence of depression.

Two psychological interventions, namely *positive fantasizing* and *mindfulness*, are core therapeutic components of multiple sessions protocolized treatments. Preventive Cognitive Therapy (PCT) delivered during the remitted phase has proven effective in lowering relapse risk [13–19]. Positive fantasizing is a core component of PCT that is aimed at challenging dysfunctional attitudes and schemas by using positive phantasy with help of imagery, enhancing positive affect and positive cognitions. Dysfunctional attitudes are attitudes or beliefs that lead individuals to engage in negative, self-referential thinking (i.e., PC) [20, 21]. By changing dysfunctional attitudes with positive fantasizing, we expect PC to change as well. Other components of PCT are enhancing positive autobiographical memories, and designing a personal prevention plan [22]. Mindfulness—which in the context of Mindfulness Based Cognitive Therapy has been shown to be effective at lowering depressive vulnerability [23–26]— aims to change dysfunctional attitudes and schemas by increasing awareness of the present moment and training an individual to disengage from automatic thought patterns (such as PC) and to develop a non-judgmental attitude towards all mental content. Both intervention techniques have proven to exert effects already in a single-session exercise. Specifically, single-session mindfulness exercises have been shown potent at reducing rumination and depressive symptoms [27, 28] and a ten-minute fantasizing exercise increased positive affect and decreased negative affect [29] in non-depressed individuals. Moreover, when contrasted with thinking after a 10-min stress-induction intervention, 10-min positive fantasizing resulted in thoughts that were less negative and more positive and less past- and more future-oriented [29]. It is however not sure whether these techniques lead to longer-lasting effects in a longer intervention.

To unravel how mindfulness and positive fantasizing affect PC in individuals vulnerable for depression, detailed measurements of the content and dynamics of PC is essential. Behaviourally, PC can be assessed by retrospective self-report covering self-assessment of cognitive behaviour on multiple timescales, using scales of rumination covering weeks (e.g., [30, 31]) or by individual momentary items (e.g., “Right now, how difficult was it to disengage from the thought?”) [32] covering minutes, respectively. Moreover, earlier studies lack task-based cognitive measures to assess PC, which could be helpful for understanding of how PC is changed on a behavioural level [32]. Moreover, PC has been found to be associated with psychological measures that may clarify the role of the central nervous system during PC. Specifically, increased heart rate (HR), reduced heart rate variability (HRV) [10, 33, 34], and aberrant brain activity [35–39] during PC was found. Therefore, HR, HRV, and electroencephalogram (EEG) may constitute (neuro)physiological measures of PC at millisecond-to-second timescales.

The current study will combine momentary-, behavioural-, cognitive-, and physiological measures at different timescales, which could give insight into the manifestations and dynamics of PC and how it can be modified by interventions. The effects of positive fantasizing and mindfulness will be contrasted by means of affect, cognition and physiology, all sampled at high temporal density, to see whether those can clarify different mechanisms for reducing PC. Whereas positive fantasizing is potent in reducing PC by using positive phantasy to enhance positive affect and positive cognitions, mindfulness focusses on increasing awareness of the present moment and is therefore potent in reducing PC. Additionally, we will characterize sleep patterns using actigraphy and self-report. Previously, PC has been found associated with poor sleep quality and sleep onset latency, which in itself can increase PC [40]. By including individual characteristic variables (such as personality, depressive history, and childhood trauma) as potential moderators of the main effect of intervention on PC, we can gain insight in what intervention works best for whom. This could be a step towards better personalized treatment [41]. The overall aim of the current study is to study the mechanisms by which mindfulness and positive fantasizing may affect the content and dynamics of PC and thereby contribute to lower depressive relapse vulnerability. The study has three objectives.

The first objective is to study the differential mechanisms by which mindfulness and positive fantasizing affect PC in individuals vulnerable for depressive relapse. To this end, we will randomize 50 remitted MDD (rMDD) individuals in a cross-over study to both mindfulness and fantasizing, with the order of interventions randomized over participants and the same duration of the interventions. We hypothesize that both techniques change PC but that they exert these effects differently. Specifically, we expect positive fantasizing to obtain its effects by increasing positive affect and changing the content of thoughts and expect mindfulness to obtain its effects by increasing focus on the present moment.

The second objective is to examine whether effects of mindfulness and fantasizing on PC in rMDD individuals differ from ND individuals. To this end, 50 ND participants will be matched to the rMDD participants and similarly randomized to undergo both mindfulness and fantasizing interventions. Comparing the effects of interventions in both rMDD and ND individuals allows us to study whether therapeutic techniques, developed and often studied in a clinical sample, work similar or different in ND individuals. Since most studies focus on the effects of mindfulness and positive fantasizing in a clinical sample [16, 19, 27, 28, 42], we hypothesize these techniques to be effective in reducing PC in rMDD individuals but expect that the interventions may show different effects on PC in ND individuals.

The third objective is to examine in an exploratory manner whether individual characteristics affect the effectiveness of the two interventions in reducing PC across all participants (i.e., what works for whom). We know from the previous literature that there is substantial variability in treatment response between MDD individuals [43,44﻿]. This variability has been suggested to be related to individual characteristics such as depressive symptoms and history, comorbid disorders/symptoms, personality traits, and cognitive dysfunction. For example, people with anhedonia may have a harder time to engage in positive fantasizing, and people with lower levels of executive functioning (mental flexibility) may find mindfulness practice difficult. Whether these independent predictors of depressive vulnerability affect intervention effects is interesting for personalized treatment purposes. This objective is exploratory, and hence we do not have specific hypotheses about the direction of these effects.

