## Methods

### Design

To examine the differential effects of mindfulness and positive fantasizing in rMDD and ND participants, we designed an open-label intervention cross-over study in which participants received both a mindfulness- and fantasizing intervention, in randomized order. The study is conducted at the University Medical Center Groningen, the Netherlands. The study includes five phases after an initial screening that is used to determine study eligibility. Eligible participants undergo 1) an assessment of baseline characteristics using self-report questionnaires (T0); 2) pre-intervention measurement 1 including one week of baseline momentary measures using Experience Sampling Methods (ESM) ten times per day, cognitive task performance two times per day, 24-h measurements of impedance cardiography (ICG)/electrocardiogram (ECG), one-week actigraphy measurements and an EEG lab measurement and questionnaires in the lab (T1); 3) peri-intervention measurement 1 where participants practice daily with an intervention and undergo the same measurements as in pre-intervention measurement 1 (T2); 3) pre-intervention measurement 2, which takes place after a wash-out period of at least one month consisting of one-week momentary measures, two-times daily cognitive task performance, actigraphy, 24-h of ICG/ECG, and EEG measurements and questionnaires in the lab (T3); 4) peri-intervention measurement 2, including practicing with the not-yet-performed intervention and the same measurements as in pre-intervention measurement 2 (T4). An overview of the study design can be found in Fig. 1.

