### Sample size

To our knowledge, we are the first to combine ESM, ICG/ECG measures, and laboratory EEG measures to study the effects of different interventions on PC. It is difficult to do power calculations for our study since there is no software available that can make predictions for our chosen statistical methods (linear mixed effect models & generalized additive models; see Statistical Analyses). We therefore calculated the sample sizes using G*Power (version 3.1.9.4) for t-tests based on questionnaire measures.

In order to study the differential effects between mindfulness and positive fantasizing on PC in individuals vulnerable for depressive relapse, we will include 50 rMDD participants. In a meta-analytic review, Perestelo-Perez et al. [49] compared the effects of Mindfulness-Based Cognitive Therapy with usual care on rumination in patients with a current depressive disorder or a depressive disorder in the past. They observed a Hedges’ *g* of -0.59 for the effect of Mindfulness-Based Cognitive Therapy compared to usual care in reducing ruminative thinking. Using G*Power 3.1.9.4, sample sizes based on these outcomes were calculated. We expect PC to reduce after mindfulness and positive fantasizing. Therefore the sample size for one-tailed t-tests was calculated. To conduct one-tailed t-tests with a statistical power of 80%, the sample size should be *n* = 36 participants. A sample size of *n* = 50 rMDD participants should therefore give sufficient power to draw reliable conclusions about treatment effects, especially since questionnaires are a less sensitive measure than most of the other measurements used in the current study (i.e., ESM, ICG/ECG and laboratory EEG). This relatively large sample size also helps us to buffer against inevitable data losses related to e.g., participants not completing all questionnaires or technical malfunctions of the physiological measurements.

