### Randomization

All participants receive both interventions, which intervention they receive first is pseudo-randomly counterbalanced across participants. Pseudo-randomization here means that individuals are randomized to either fantasizing or mindfulness as first intervention by order of inclusion. Specifically, every three weeks a new measurement session starts. Mindfulness and fantasizing alternate in three-week blocks. New sign-ups in this three-week block are allocated to mindfulness or fantasizing, in alternating order.

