### Strengths

Our study is the first cross-over trial that includes several measurements at baseline and during intervention performance to track the underlying mechanisms of change of PC by therapeutic techniques, derived from existing therapies, in the vulnerability for depression. In a cross-over study design, participants are their own control, reducing the variability between groups and allowing for within-subject comparisons. By combining measurements in participants’ daily life (ESM), questionnaires, cognitive task, and physiological measurements at baseline and during intervention performance, we can get a detailed overview of how PC is affected by interventions on a behavioural, physiological, and cognitive level at different timescales. Several researchers have addressed the importance of within-subject analyses in psychiatry combing subjective and objective measurements [75, 76]. Moreover, the importance of studying the mechanisms of effects of existing psychological treatments has been addressed by several researchers [77]. Another strength of the study is the sample selection. We select our sample based on recent depressive episodes, current medication use, and previous experiences with mindfulness and/or positive fantasizing. Therefore, we study a sample that is highly vulnerable for depressive relapse in which confounding variables such as medication use and previous experiences are excluded. Furthermore, we are including baseline questionnaires capturing individual characteristics that might predict treatment effectiveness, allowing us to not only study the effects of the interventions but also what works best for whom.

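### With no untreated sequence and the intervention week always second, the design can show how the two techniques differ but not that either one reduces perseverative cognition

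*Protocol article*

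**What the plan says.** The article describes two active sequences and nothing else. Under Randomization: "All participants receive both interventions, which intervention they receive first is pseudo-randomly counterbalanced across participants". Under Design the study is "we designed an open-label intervention cross-over study in which participants received both a mindfulness- and fantasizing intervention, in randomized order". The never-depressed group is treated in the same way (Background, second objective).

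The order of measurement is fixed within each period. According to the Abstract (Methods), the measures "are performed during the week before (pre-) the interventions and the week during (peri-) the interventions", and the same order is repeated after a wash-out of at least one month. Design describes the first intervention week as "peri-intervention measurement 1 where participants practice daily with an intervention and undergo the same measurements as in pre-intervention measurement 1".

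Alongside the differential aim, the article states expectations about each technique in its own right:
- Background, first objective: "We hypothesize that both techniques change PC but that they exert these effects differently".
- Background, second objective: "we hypothesize these techniques to be effective in reducing PC in rMDD individuals".
- Sample size: "We expect PC to reduce after mindfulness and positive fantasizing", which is the reason given for a one-tailed calculation.

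Outcome measures names within-subject pre-to-peri changes as the primary outcomes for aim 1, and differences between the groups in those changes as the primary outcomes for aim 2. The tests in Statistical analyses are narrower: intervention by session by time for aim 1, intervention by session for the questionnaires, and group by session by intervention for aim 2. Strengths says: "In a cross-over study design, participants are their own control". Challenges mentions the pandemic and participant burden, but not the absence of an untreated comparison.

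**The concern.** Saying that a technique is effective in reducing perseverative cognition (PC) compares it with not using it, and no such comparison exists here. Session (pre or peri) coincides with measurement order in every person and both periods. Randomizing which technique comes first does not vary that order.

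The intervention week follows a week of ten prompts and two task runs a day, about 60 minutes daily by the article's own account, in an open-label study. Ratings may move for reasons unrelated to the technique: self-monitoring, rating fatigue, task practice, expectation, or the natural course of mood. The movement could be up or down.

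At stake is the wording of the conclusion. A fall from pre to peri could be read as support for the stated hypothesis that short exercises reduce PC in people at risk of relapse. A larger fall in one group could be read as greater effectiveness there. The design supports neither reading.

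**Working it through.** **1. What the design identifies.** Let C be a person's pre-to-peri change in group g, under technique k, in period p. Write its mean as T(g,k) + D(g,p), where T is the intervention effect and D is everything else that moves ratings between the two weeks, taken as equal for both techniques.

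- Mindfulness minus fantasizing, sequence mindfulness first: T(g,M) − T(g,F) + [D(g,1) − D(g,2)].
- The same contrast, sequence fantasizing first: T(g,M) − T(g,F) − [D(g,1) − D(g,2)].
- Average of the two sequences, equally filled: T(g,M) − T(g,F). Drift has gone, whatever its size in group g.
- Difference of that contrast between groups (group by session by intervention): drift has gone here too, even if D is larger in remitted participants.
- Change averaged over techniques: mean of T(g,M) and T(g,F), plus mean of D(g,1) and D(g,2). Drift stays.
- Group difference in that average (group by session): difference in mean T plus difference in mean D. Drift stays if it differs by group.

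So the tests in Statistical analyses are protected from drift shared by the techniques. The expectations about each technique, and the raw changes listed in Outcome measures, are not.

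**2. The plan's own figure.** Sample size takes g = −0.59 from a meta-analytic comparison of mindfulness-based cognitive therapy with usual care, one-tailed, 80% power, and arrives at n = 36. Alpha is taken as 0.05.

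- Two independent groups, normal approximation: n per group = 2 × (1.6449 + 0.8416)² / 0.59² = 12.365 / 0.3481 = 35.5, so 36. The exact t version gives 36.22, so 37.
- Paired or one-sample, exact t: 19.19, so 20.

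The stated 36 matches the two-group calculation. It therefore rests on a contrast with usual care, which this trial does not contain.

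**3. Illustration with assumed drift.** Inputs: n = 50, true intervention effect zero, one-sided 5% test of pre-to-peri reduction. Drift is a downward shift in units of the SD of the change score. The noncentrality is drift × √50, with 49 degrees of freedom; at 0.3 it is 0.3 × 7.07 = 2.12.

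| Assumed drift | Probability of a significant reduction |
|---|---|
| 0 | 5% |
| 0.1 | 17% |
| 0.2 | 40% |
| 0.3 | 67% |
| 0.4 | 87% |
| 0.5 | 97% |

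In 20,000 simulated cross-overs with drift 0.3 in both periods and no intervention effect, each technique appeared effective in about 67% of trials, and the between-technique contrast was significant in 5.1%. With unequal drift by period (0.5 then 0.2) the contrast was significant in 4.5%. Upward drift would work the other way and hide a real reduction.

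**The case against.** The strongest reply is that the planned inference is already differential. No pre-to-peri main effect is named as a test of effectiveness. The one-tailed test appears only as a proxy for sample size, chosen because the authors found no software for their models. Aims and design are framed as a comparison of mechanisms, with technique-specific predictions such as more present-moment thought under mindfulness but not fantasizing. Common drift would not produce that difference. This stands, and it limits the point to what may be concluded from the common change.

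Three stronger readings are tempting and not supported:
- A reader might infer that larger drift in remitted participants would bias the aim 2 test. The stated test is group by session by intervention, in which such drift cancels if it is equal under both techniques. Only the looser outcome wording, the group difference in raw change, is exposed.
- A reader might infer that regression to the mean favours a false reduction. Nobody is selected for high PC. Entry caps depressive symptoms (IDS-SR30 of 21 or lower in the remitted group; above 13 excluded in controls). If PC tracks symptoms, this would push later scores up, so the direction is open.
- A reader might take the percentages above as the trial's error rate. They belong to a test that the article does not plan, at drift sizes that it does not give.

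The second intervention-free week (T3) also carries some information, since drift that simply accumulates would not reset there. But it follows the first intervention, so it mixes drift with carry-over and cannot replace an untreated comparison.

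**Conclusion.** The point holds in a limited form. The between-technique contrast, and its difference by group, remain interpretable as intervention effects as far as this point goes. That assumes drift and expectation are alike under both techniques, sequences are about equally filled, and the first intervention does not carry over. The statements that each technique changes or reduces PC, and the raw pre-to-peri changes or group differences in them, cannot serve as evidence of effectiveness. The size and direction of any distortion are unknown because the documents give no drift figure; the 17% to 97% range only shows that a drift of 0.1 to 0.5 SD would matter at n = 50. The correction should be made because it changes what the trial may conclude, although it changes none of the planned tests.

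**What to change.** 1. In Background and Sample size, state that the only causal intervention effect claimed is the difference between techniques in pre-to-peri change, together with its difference between groups.
2. In Outcome measures, label the pre-to-peri change common to both techniques, and the group by session difference, as uncontrolled and descriptive.
3. When the common change is reported, show beside it the trend within the intervention-free weeks (for example, first against second half of T1 and of T3) by group, noting that T3 may carry over from the first intervention.
4. In Strengths, limit the own-control statement to the between-technique contrast. In Challenges, add the missing untreated comparison.

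The cost is wording and one descriptive analysis of data already being collected. No new arm or participants are needed. The downside is a weaker claim about each technique on its own.
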